#### Semi-structured questionnaire and process evaluation

The qualitatively obtained data from the semi-structured interview will be transcribed verbatim. Two independent researchers will perform deductive content analysis of the transcribed text using ATLAS.ti. Conceptual labels will be assigned to textual fragments and organized into categories. Categories will be merged into common themes in a consensus meeting. Disagreements will be solved through discussion. The quantitative items scored by coaches will be calculated by means of descriptive statistics.

### Monitoring and participant safety

Monitoring of the recruitment and execution of the study will be conducted by the trial monitoring committee of the MUMC+ (Clinical Trial Center Maastricht). Adverse events (AEs) and serious adverse events (SAEs) are not anticipated but cannot be ignored. If participants drop out, they will be asked if they had experienced an adverse or harmful event during the study period that could be attributed to “Partner in Balance.” Included participants will be asked the same question during the post-intervention assessment and at the 3-, 6- and 12-month follow-ups. All AEs and SAEs will be recorded. SAEs will be reported to the accredited Medical Ethics Committee that approved the protocol. AEs will be followed until they have abated or until a stable situation has been reached. Depending on the event, follow-up may involve additional tests or medical procedures, as indicated, and/or referral to the general physician or a medical specialist. If participants do not agree to this procedure, they cannot participate in the study.

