### Randomization

Following the baseline assessment, participants will be randomly assigned to either the self-management intervention or the waiting-list control group using a computer program operated by an independent statistician. Block randomization will be conducted to reduce the risk of unbalanced assignment to the experimental and control groups. We will use randomly permuted blocks and several block sizes (4, 6 and 8). The block size and order of allocation will be randomly chosen at the beginning of each block. This reduces the risk of predicting group assignment and keeps research staff blind to the randomization process. An independent research assistant who is unknown to the allocation of the treatment will conduct the post-intervention and follow-up assessments, and will be asked to evaluate the success of blinding, and reasons for possible unmasking, on the Case Record Form.

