#### Control group

Participants in the control group will be placed on a waiting list for 8 weeks. After they complete the post-test assessment, they will receive the online self-management intervention. They will receive the same pre-test and post-test attention from the research team as the experimental group.

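### The only harm question described asks for events blamed on the programme, so elicited harms in the waiting-list period (T0–T1) cannot be validly compared between arms

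*Protocol article*

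**What the plan says.** **Harm question** (Protocol article, Monitoring and participant safety). Of participants who drop out, the section says "they will be asked if they had experienced an adverse or harmful event during the study period that could be attributed to" the programme. For everyone still in the study: "Included participants will be asked the same question during the post-intervention assessment and at the 3-, 6- and 12-month follow-ups". The same section promises, without qualification, "All AEs and SAEs will be recorded", and says that SAEs go to the ethics committee. It describes no other way of eliciting events.

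**Exposure of controls** (Control group). Controls first spend 8 weeks waiting, without the programme. On what follows, the section says: "After they complete the post-test assessment, they will receive the online self-management intervention".

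**Visit labels** (Procedure). T1, at 8 weeks, is the post-intervention visit for the programme arm and the waiting-list visit for controls. T2, 8 weeks later, is the post-intervention visit for the waiting-list arm.

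**Masking** (Randomization). "An independent research assistant who is unknown to the allocation of the treatment will conduct the post-intervention and follow-up assessments". The same person "will be asked to evaluate the success of blinding, and reasons for possible unmasking, on the Case Record Form".

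**The concern.** The question asks the participant to judge causality before anything is noted. This has two consequences. First, an event that the participant does not connect with the programme is not elicited, in either arm. Second, controls have no programme to connect an event with until after T1, so the question does not work in the same way in the two arms during the period that randomisation protects.

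Harm is not far-fetched on the protocol's own account. The Background accepts that support in early dementia can be experienced badly when it does not fit the caregiver's situation or the stage of disease. A caregiver whose mood worsens may not link this to an online module. What is at stake is whether the trial can describe, like for like, what happened to caregivers with and without the programme.

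There is also a lesser worry. The question is placed within assessments conducted by a masked assistant, and some answers would disclose the arm.

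**Working it through.** The plan gives no figure for harms, so there is none to reproduce. The check sets the sections side by side.

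**1. Which period allows a comparison with unexposed participants?** Under Control group, controls are offered the programme once their post-test is done. Both arms have therefore been offered it after T1, and T0–T1 is the only randomised, unexposed comparison.

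**2. What does the harm question yield for that period?** The term post-intervention assessment can be read in two ways.

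| Reading | Programme arm at T1 | Control arm at T1 |
|---|---|---|
| It means T1 in both arms | Asked; attributable events can be reported | Asked about a programme not yet received; a truthful count is 0 |
| It means T1 for the programme arm and T2 for controls, following the Procedure labels | Asked | Not asked; no count exists |

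On the second reading, asking at T1 in one arm only would also require whoever asks to know the allocation.

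**3. Can later visits fill the gap?** No. The question refers to the whole study period, but it still admits only attributable events. What controls report from T2 onwards relates to their own exposure after T1.

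**4. What would the elicited contrast estimate?** Take 40 planned participants per group (Sample size) and ignore dropout. Let p₁ and p₀ be the true proportions with an event during T0–T1 in the programme and control arms, and let f be the fraction of programme-arm events that participants attribute to the programme.

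- Expected elicited count, programme arm: 40 × p₁ × f
- Expected elicited count, control arm: 0 (first reading) or undefined (second reading)
- Expected difference, first reading: 40 × p₁ × f − 0 = 40 × p₁ × f

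The control rate p₀ does not appear. With p₁ = p₀ the elicited counts still differ whenever p₁ and f are above 0. With f near 0 a real excess would not show. The documents give no value for p₁, p₀ or f, so none is assumed here.

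**5. Does the question match the recording promise?** Recording all AEs and SAEs requires a route for events that the participant does not attribute. The question supplies none, so for such events the promise depends on unsolicited reports.

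**6. Could the question unmask?** The masked assistant conducts the assessments, and the question falls during them. The article does not say who puts the question, or whether it comes before or after the outcome measures. If the assistant asks it, a reply that the programme has not started, or a complaint about a module, would disclose the arm. The Case Record Form item would register this but not prevent it.

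**The case against.** The strongest case on the other side is that the plan is not blind to harm in T0–T1.

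- **Symptom scales.** The plausible harms of a low-intensity psychosocial programme are worse mood, anxiety, stress or quality of life. The CES-D, HADS-A, PSS and ICECAP-O measure these without attribution, and each outcome is compared between arms post intervention. This stands, and it rules out the tempting reading that the trial yields no comparative safety data. Group means on scales do not replace a count of discrete events, however.
- **Resource use.** The RUD-lite covers hospital care, professional contacts and nursing-home admission from baseline to 12 months, again without attribution. This too stands in part. It is a costing instrument, and the article does not link it to AE reporting.
- **Recording.** The article says that all events are recorded. A reader might infer that unattributed events are lost. The documents do not support that, because unsolicited reports may be recorded in both arms. The defect is in what is elicited.
- **No comparison planned.** The statistical section contains no between-arm AE analysis, so there is no planned analysis that would be biased. This stands, and step 4 above describes only what such a contrast would mean if someone made it.
- **Masking.** A reader might infer that assessor blinding is undermined at the primary endpoint visit. The documents do not show this. Who asks, and when, is not stated; AEs are not anticipated; and both primary outcomes are questionnaires answered by participants who know whether they have had the programme, which limits the assessor's influence.
- **Missing schedule.** The figure with the schedule per condition is not available here and might settle which reading of post-intervention assessment applies. The conclusion does not depend on it, because both readings fail.

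**Conclusion.** The point holds as a defect of harm ascertainment. The elicited harm data for T0–T1 contain no usable control count: it is zero by construction or absent for all 40 planned controls, whatever their true event rate. They therefore cannot support a valid comparison between arms. The question alone also cannot deliver the stated recording of all AEs and SAEs.

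This rests on three assumptions: the question is asked as the article words it, controls answer truthfully, and controls have no access to the programme before T1. It does not touch the sample size or the efficacy analyses. Its practical weight is moderate, since the symptom scales, the RUD-lite and unsolicited reports capture some harm without attribution. Unmasking is a secondary risk that follows only if the masked assistant asks the question.

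**What to change.** 1. Replace the attribution question with one allocation-neutral question about any adverse or serious event since the last assessment. Use identical wording in both arms at every assessment, including T1 and T2, and use the same wording for dropouts.
2. Place it after the outcome questionnaires, so that an answer that discloses the arm cannot affect outcomes already collected.
3. Have relatedness recorded separately by someone other than the masked assessor, preferably someone who does not deliver the programme.
4. Tabulate T0–T1 events by arm, descriptively and without a test.

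**Cost.** The form needs one reworded and repositioned item, a person to record relatedness, and one table. Visits and sample size do not change. The real burden is that more unrelated events will be recorded, and the article commits the study to following AEs until they resolve or stabilise. Recruitment began in September 2014 and is ongoing, so participants already assessed will have answered the old question. The table should show which wording each participant received.

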## Discussion

In this paper, we described the design of a randomized waiting-list controlled trial to evaluate the effectiveness and process of a blended self-management program to improve caregiver self-efficacy and psychological well-being. As recommended by the MRC Framework [27], this study was preceded by an iterative development and feasibility study [28]. There are several unique aspects of the current study. To our knowledge, this is the first blended care intervention for early-stage dementia caregivers developed with potential users and tailored to the individual user.

Furthermore, the MRC Framework suggests that implementation should be considered during the first phases of intervention development and evaluation [27]. Implementation is expected to be successful because this intervention was developed with potential professional users and will be evaluated in multiple institutions and with coaches from different backgrounds. The program will be delivered in daily practice and can be integrated in the present care provided. Furthermore, tailoring to individual caregiver needs is expected to increase program effectiveness [17] and facilitate implementation [57]. Additionally, the GAS enables identification of individual benefits that caregivers experience beyond the generalized measures [58]. The process evaluation facilitates our understanding of the quantity and quality of intervention delivered and evaluates the generalizability of the research based on an understanding of the context [59]. The mixed-methods approach enables better understanding of whether and how the intervention works, and facilitates replication of the intervention through greater knowledge of the active component(s) and potential barriers to implementation [60]. Because all the resources used, costs and outcomes are transparently listed in the cost-consequence analysis, decision-makers can select the information that is of most interest to them. Finally, the waiting-list controlled design of the study allows all potentially interested participants to participate in the intervention program. It may increase caregivers’ motivation to participate given that usual care for (very) mild dementia caregivers often either does not include counseling or includes only very infrequent counseling [61].

In conclusion, the results of this study will be a valuable contribution to the growing knowledge on e-health for dementia caregivers. “Partner in Balance” is expected to be effective in increasing caregiver self-efficacy and reducing depressive symptoms in early-stage dementia caregivers. The study will also provide insight into program delivery and program costs related to the program consequences. The results will be used to inform clinicians and researchers of the delivery, costs and effects of “Partner in Balance” as a tool to support dementia caregivers.

### Trial status

Participant recruitment for this study commenced in September 2014, and the study is currently recruiting early-stage dementia caregivers.

## Abbreviations

CONSORT: Consolidated Standards of Reporting Trials
MRC: Medical Research Council
SPIRIT: Standard Protocol Items: Recommendations for Interventional Trials
